# Implementation of a Primary Prevention Program for Posttraumatic Stress Disorder in a Cohort of Professional Soldiers (PREPAR): Protocol for a Randomized Controlled Trial

**DOI:** 10.2196/47175

**Published:** 2024-01-26

**Keywords:** posttraumatic stress disorder, military, primary prevention, biopsychosocial, resilience, coping, stigma, biophysiology, PTSD, implementation, soldier, veterans, prevention program

## Abstract

**Background:**

Posttraumatic stress disorder (PTSD) is a psychiatric disorder that can manifest after a traumatic event where the individual perceives a threat to his or her life or that of others. Its estimated prevalence in the European population is 0.7% to 1.9%. According to the “dose-response” model, individuals who are most exposed to traumatic events are most at risk of developing PTSD. Hence, it is unsurprising that studies have observed a higher prevalence among the military population, ranging from 10% to 18%, or even up to 45%. This project’s overall goal is to evaluate the primary prevention actions that can strengthen the resilience of at-risk professionals, notably military personnel, in the short term, with the medium- to long-term aim of preventing the occurrence of PTSD and improving the patient’s prognosis.

**Objective:**

This study’s objectives are (1) to design a primary prevention program for PTSD, tailored to the studied military population and compatible with operational constraints; and (2) to implement and validate the Primary Prevention of Posttraumatic Stress Disorder in Military Professionals (PREPARE) program in the short term with operational personnel belonging to the French Mountain Infantry Brigade.

**Methods:**

This is a single-center, prospective, randomized, parallel-group controlled cohort study. The cohort is divided into 2 groups: the nonintervention group receives no training, and the intervention group follows a dedicated prevention program (structured into 8 workshops and 2 debriefing and practice reinforcement workshops). Each participant is evaluated 4 times (at inclusion, +4 months, +6 months, and +12 months). During each visit, participants complete several psychosocial questionnaires (which take 15-80 minutes to complete). Samples (a 30-mL blood sample and three 5-mL saliva samples) are collected on 3 occasions: at inclusion, +4 months, and +12 months. Emotional reactivity (electrocardiogram and electrodermal activity) is measured before, during, and after the classic and the emotional Stroop task.

**Results:**

The project is currently ongoing, and results are expected to be published by the end of 2024.

**Conclusions:**

The study adopts an integrative approach to the processes that play a role in the risk of developing PTSD. Our biopsychosocial perspective makes it possible to target levers related to factors specific to the individual and socio-professional factors. The following dimensions are addressed: (1) biophysiology (by studying markers of the neurobiological stress response, wear and tear, and vulnerability phenomena and reinforcing the flexibility of the autonomic nervous system), (2) psychology (by facilitating and measuring the development of flexible coping strategies to deal with stress and evaluating the moderating role of the individual’s sense of duty in the development of PTSD), and (3) social (by facilitating community strategies aimed at reducing stigmatization and supporting the use of care by professionals in difficulty, in the institutional context).

**Trial Registration:**

ClinicalTrials.gov NCT05094531; https://clinicaltrials.gov/study/NCT05094531

**International Registered Report Identifier (IRRID):**

DERR1-10.2196/47175

## Introduction

### Background and Rationale

#### Overview

Posttraumatic stress disorder (PTSD) is a psychiatric disorder that manifests following the experience of a traumatic event (TE) where the individual has perceived a threat to his or her life or that of others [1]. In France, it is considered to be the third most widespread psychiatric disorder, after major depression and specific phobias. Its prevalence in the European population is estimated to be between 0.7% and 1.9% [2,3]. According to the “dose-response” model, individuals who are most exposed to TEs are most at risk of developing PTSD [3-5]. At-risk occupations, such as the military, law enforcement, and first responders, carry an inherent risk of experiencing trauma. Hence, it is unsurprising to observe a high prevalence of PTSD in military populations, ranging from 10% to 18% or reaching up to 45% [5-9], depending on the study. Although cumulative exposure seems to be an important determinant in the general population [10], the literature does not establish a clear link among at-risk professionals. Nevertheless, it is reasonable to think that cumulative exposure is detrimental, and may even lead to fragilization, which would be consistent with the intensity of PTSD symptoms [11,12]. Repeated exposure triggers a reaction that builds on the consequences of previous exposures, increasing the complexity of the link between cumulative exposure and PTSD development, via multiple pathways.

#### PTSD Prevention

New medical research has influenced public policy, and the promotion of good health has become a key priority where policies seek to encourage certain behaviors that protect, improve, or restore the health of individuals, groups, or the entire population, while a prevention framework is used when the goal is to limit or prevent the development of a specific disease.

In the 1980s, evidence-based medicine emerged. The approach is founded on the principle of structuring prevention and public health decisions based on scientific evidence (eg, epidemiological studies and systematic clinical studies). A given health problem can be addressed by preventive interventions at primary, secondary, or tertiary levels. The objective of primary prevention is to intervene before the problem occurs; actions target the determinants of the problem by reducing risk factors or by promoting or reinforcing protective factors. In the context of PTSD, primary prevention can intervene at the level of preventing the trauma or at the level of PTSD prevention after the TEs. For at-risk professions in particular, PTSD prevention is the primary target, as the risk of exposure to trauma is integral to the profession. Secondary prevention seeks to define interventions once the problem is identified; it consists of early detection and referral for treatment (ie, after exposure to a TE). Finally, tertiary prevention seeks to manage the problem and prevent relapse. If necessary, the goal is to treat or limit any aggravation of the problem, notably any psychosocial consequences or comorbidities associated with PTSD. At all 3 levels, prevention must respect individual freedom [13].

#### Primary Prevention of PTSD

Effective primary prevention relies upon a sound theoretical understanding of the processes and determinants of the problem, knowledge of actions that have been scientifically validated in other populations, and clinical expertise in the field, which reflects the characteristics (eg, sociocultural) of the target population. This “selective prevention” approach seeks to target exposed participants.

In the domain of PTSD, primary interventions are rare, as such actions aim to prevent the impact of TEs before they occur. Nevertheless, this literature [14] gives us an insight into the potential effects of cumulative exposure to TEs during the career of military professionals. In this context, primary prevention interventions target several determinants that contribute to developing resilience following the TE. The approach underlines the need to characterize the factors that support individual and collective resilience processes, tailored to the characteristics of the population of at-risk professionals. This initial step is a prerequisite to the definition of relevant targets and the development of an appropriate prevention intervention for the population.

The proposed program (which we call Primary Prevention of Posttraumatic Stress Disorder in Military Professionals [PREPAR]) is part of a comprehensive prevention approach that synergistically links physiological, psychological, and social determinants. The approach stems from the etiological model proposed by Jones and Barlow [15]. This model is a comprehensive framework used in clinical psychology to understand the development and maintenance of psychological disorders, particularly PTSD. It integrates various factors that contribute to the onset and perpetuation of these disorders. Several etiological factors, including biological, cognitive, and behavioral components, are implemented in this model. The model also takes into account predisposing factors and moderating variables. It emphasizes a holistic approach to understanding mental disorders, taking into account the complexity of the human experience.

#### The Physiological Dimension

PTSD is described as a failure of emotional extinction which develops following exposure to intense fear. Exposure to a stressful event leads to a neurobiological stress response, resulting in the activation of the sympatho-adrenergic neurovegetative system and the corticotropic neuroendocrine axis. Although this dual physiological response is effective in the short term, it comes with a biological cost; regulatory mechanisms aim to compensate for this loss by supporting poststress recovery. A repeated inability to recover and extinguish the stress response in the long term (repeated exposures over a short time period) creates a so-called “allostatic load” [16], which progressively limits the flexibility of the central and peripheral nervous system. The peripheral nervous system is of particular interest, due to its role as a mediator of the allostatic load. The parasympathetic branch plays a role in the emotional extinction and correction of the load, making it a key vulnerability factor for health when it is insufficiently effective [17]. Certain professions (frontline responders and military personnel) are at risk of developing a significant allostatic load, due to their repeated exposure to TEs (inherent in the nature of their work). On top of this, personnel must adapt, on a daily basis, to various environmental demands: physiological (sleep debt, altered sleeping patterns, etc), physical (hypoxia, etc), and cognitive and emotional (traumatic exposure, etc), among others. All of these factors test the flexibility of the individual’s physiological systems, particularly the autonomic (ie, parasympathetic) nervous system, which, consequently, appears to be a key target for prevention measures.

#### The Psychological Dimension

Military personnel participate in multiple missions in conflict zones, and this is likely to alter the flexibility of their executive and emotional regulation functions. Although training programs aim to develop automated responses to well-known mission scenarios, they do not focus on developing the change in viewpoint that contributes to the resilience process. Moreover, preclinical data show that both acute and repeated stress are likely to reduce cognitive flexibility [18,19]. A slight reduction in cognitive flexibility likely reduces the flexibility of emotional regulation strategies following a TE, thus increasing the impact of exposure. This hypothesis draws upon the notion of “coping flexibility.” The latter concept represents the individual’s ability to evaluate the effectiveness of his or her strategies for coping with stress in a specific situation and then adopting alternative strategies, if necessary [20]. The evaluation of training in the diversification of emotional regulation strategies in military populations has found a reduced risk of PTSD after exposure to TEs. Furthermore, a relationship has been identified between cognitive flexibility and self-compassion [21]. The data also suggest that increasing self-compassion contributes to increasing cognitive flexibility [22].

Finally, a clear sense of duty has been found to counterbalance perceived constraints associated with the mission [23,24]. The literature reports that the meaning attributed to the work environment can, to a significant degree, compensate for the perception and impact of occupational stressors [25].

#### The Social Dimension

The social dimension targets normative pressure and stigmatization. These determinants are specific to the institutional context of military personnel and may represent risk factors. Thus, normative group pressure to follow codes that encourage the nonexpression of emotions [26] can be a risk factor, as military personnel can be reluctant to speak about their psychological and somatic symptoms, which delays treatment. A fear of stigmatization by the institution and peers is another potential barrier to care. Overall, these social factors are obstacles to both individual and collective positive health behaviors.

### Research Hypotheses

#### Overview

The goal of this project is to evaluate a multidimensional biopsychosocial primary prevention intervention for PTSD aimed at strengthening the resilience of at-risk professionals, namely military personnel, in order to prevent the occurrence of PTSD or reduce its severity.

The objectives of the project are as follows: (1) to design a primary prevention program for PTSD specific to the studied military population and compatible with operational constraints; (2) to implement or validate the program with operational personnel belonging to the French Mountain Infantry Brigade (*Brigade d’Infanterie de Montagne*); and (3) to understand PTSD and its prevention from 3 perspectives: biophysiological (by studying key markers of the neurobiological stress response, strain and vulnerability and increasing the flexibility of the autonomic nervous system); psychological (by facilitating and measuring the development of flexible strategies to cope with stress and evaluating the moderating role of the meaning of the mission in the development of PTSD); and social (by facilitating community strategies aimed at reducing stigmatization and helping professionals in difficulty to access care in the institutional context).

Our biopsychosocial approach adopts an integrative understanding of the processes at play in the risk of developing PTSD. This perspective makes it possible to target levers related to factors specific to the individual (at physiological and psychological levels), and contextual and social factors (related to the working environment).

#### The Physiological Dimension

The change in parasympathetic vagal flexibility is an early and silent sign of physiological deterioration. It can be identified by noninvasive measurements (resting or tonic heart rate variability, and activation or phasic heart rate variability) and modulated by exercises that target vagal activity (cardiac coherence techniques), which can be easily integrated into a busy professional agenda. A preliminary feasibility study among a group of firefighters (SDIS 73) demonstrated very good acceptance of this technique by the selected professionals and good adoption in daily life [24].

#### The Psychological Dimension

Two factors are targeted in the psychological dimension: coping flexibility and the sense of duty. These 2 determinants have rarely been targeted in studies of the prevention of occupational PTSD. The focus on coping flexibility and self-compassion seeks to improve emotional regulation, and the focus on the sense of duty seeks to target the silent determinants of occupational PTSD, with the overall aim of identifying an effective primary prevention intervention.

#### The Social Dimension

The targeted determinants are the beliefs and socio-normative processes that play a role in PTSD in a military population (self-stigmatization, stigmatization by others, normative pressure, and group cohesion). The intervention aims to establish a dedicated space to normalize the discourse, with the overall aim of discussing PTSD and making it visible, along with the signs of emerging psychological and somatic injuries. Specific group facilitation techniques are used, notably social modeling, which aims to reinforce feelings of self-efficacy that support the public expression of signs of injury and to support the search for appropriate care, when necessary [27].

### Objectives of the Research

The main objective is to determine the effectiveness of a biopsychosocial program targeting the resilience (developing stable resources to adapt to occupational demands, in order to cope with TEs) of military personnel in the context of PTSD prevention.

The secondary objective is to better understand interindividual variability regarding the program’s impact. We will study levels of vulnerability at inclusion and their impact on the program’s effectiveness. We will also track postprogram changes in resilience (at 6 and 12 months). In addition, we will evaluate (1) the impact of the program on activation and psychobiological deterioration biomarkers and (2) the psychosocial determinants at 4 months (the end of the program) and 12 months (to evaluate persistence). In addition, we will measure adherence to the intervention at group and individual levels, through an evaluation at the end of the program. Finally, we will examine user satisfaction with the URGOfeel sensor and its application during workshops.

## Methods

### Ethical Considerations

Prior to their participation in the study, all participants will receive 2 separate notifications: one detailing the primary study and the other focusing on the genetic part. It is essential to emphasize that participation in the genetic segment is entirely optional, allowing individuals to engage solely in the main study if they prefer. Both of these notifications provide comprehensive information about the study’s objectives, limitations, and legal requirements, especially in terms of privacy and confidentiality. Additionally, they clearly outline the potential benefits and risks associated with participation.

All collected data will undergo rigorous anonymization and processing in strict accordance with the MR001 reference methodology, in compliance with the regulations of the French Data Protection Authority (CNIL).

Our study maintains a steadfast commitment to ethical standards, in alignment with the principles set forth in the 1964 Helsinki declaration and its subsequent amendments. Furthermore, the ethics committee of Ile de France 8 formally approved the research protocol on January 12, 2021 (reference 20.12.10.58611). It is important to note that participants will not receive any form of compensation for their participation in this research.

### Recruitment

The study will be conducted with members of the 27th Mountain Infantry Brigade, located in the Auvergne-Rhône-Alpes region of France. Participants will be recruited from companies proposed by the Brigade’s line manager, depending on the ability to operationalize and implement measurement sessions, and the intervention.

### Randomization

Individual randomization is not feasible for two reasons: (1) the logistics involved in deploying the training program and the availability of participants; and (2) the need to avoid a contagion effect between members of the Brigade who benefit from the program and those who do not.

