**Figure 1 figure1:**
[figure not shown]
Study timeline. *: 2 to 3 hours to take measurement; △: “debriefing and anchoring of the practice” workshop.

**Table 1 table1:** Summary of the stages of the study.

	Visit 1 inclusion	+4 months	+6 months	+12 months
Information – consent	✓			
Sociodemographic data	✓			
Self-administered questionnaires	✓	✓	✓	✓
Blood and saliva collection (physio-biology and genetic)	✓	✓		✓
Emotional reactivity	✓	✓		✓
“Debriefing and anchoring of the practice” workshop			✓	✓

The first step is a briefing session with 2 of the Brigade’s companies. Each individual will receive 2 information letters (1 regarding participation in this study, and 1 regarding participation in genetic studies), in order to allow time to reflect before the inclusion visit.

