### Statistical Methods

Continuous variables will be presented as mean and SD, if the distribution is normal (the Shapiro-Wilk test will be used, if necessary). In case of a nonnormal distribution, data will be presented as median, quartiles, and extreme values. Scale variables will be treated as ordinal data and analyzed as above. Depending on the analysis, data may be classed as categorical variables. Categorical variables will be expressed as absolute values and percentages. To control for attrition, calculations will assume 20% of data are missing.

The primary analysis will examine the effectiveness of the prevention program. This will be evaluated by comparing the percentage of responses between intervention and nonintervention groups, using a *χ*^2^ test. Secondary analyses will examine the abovementioned markers. Values for the intervention and the nonintervention group will be compared using a repeated measures ANOVA if the conditions for applying an ANOVA are met. Vulnerability will be initially identified using a cluster analysis of the measured biological variables (a *k*-means or Gaussian model mixture, depending on the distribution). The analysis will seek to identify the most biologically at-risk cluster (vulnerable compared with nonvulnerable). The effect of the intervention as a function of vulnerability status will be evaluated using repeated measures ANOVA, by comparing vulnerable and nonvulnerable groups. Psychosocial variables will be compared between intervention and nonintervention groups using repeated measures ANOVA, if the conditions for its application are met. A regression analysis will aim to test the mediating role of psychosocial determinants in the improvement of the composite score.

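### The trial is labelled randomized but appears to be allocated by group, probably one company per arm, while the sample size and primary chi-square treat soldiers as independently randomized

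*Protocol article*

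**What the plan says.** The protocol article presents the study as randomized in two places: the title ("Protocol for a Randomized Controlled Trial") and the Methods part of the abstract ("This is a single-center, prospective, randomized, parallel-group controlled cohort study").

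The Randomization section is two reasons long. It opens with "Individual randomization is not feasible for two reasons", cites logistics and availability first, and then "the need to avoid a contagion effect between members of the Brigade who benefit from the program and those who do not". It describes no draw, no unit of allocation and no number of units.

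Three other places bear on how the arms were formed:

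- Recruitment: "Participants will be recruited from companies proposed by the" Brigade's line manager, according to whether sessions and intervention can be put into operation.
- Participant Timeline, below Table 1: "The first step is a briefing session with 2 of the" Brigade's companies.
- Abstract, Methods: "The cohort is divided into 2 groups: the nonintervention group receives no training", the other group following the program.

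The statistics are at the level of the individual. Statistical Methods sets the primary analysis as "comparing the percentage of responses between intervention and nonintervention groups", with a chi-square test. Sample Size is a two-proportion calculation: 55% against 30% responders, two-tailed, power 0.80, 20% dropout, 58 per group and 116 in all. Neither section mentions an ICC, a design effect or a cluster. The limitations in the Discussion deal with adherence and operational constraints, not with company differences.

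**The concern.** These statements do not fit together. If individuals were not randomized, the arms were made from groups of soldiers. Two companies, two arms and a wish to keep trained and untrained soldiers apart point to one company in each arm.

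Soldiers of one company share command, workload and cohesion. The protocol treats such factors as determinants: it targets group cohesion and normative pressure, measures vertical and horizontal cohesion, and delivers the program in group workshops. Outcomes within a company are therefore unlikely to be independent.

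Two things are at stake. The first is the standard error: the chi-square omits variance between groups, so it rejects a true null hypothesis too often. The second applies only with one company per arm. A difference between arms is then also a difference between companies, and no analysis of the data can separate the two. A change of command, workload or training in one company during the four months could move self-reported affect, self-compassion and hardiness as the program would.

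**Working it through.** **Inputs.** From Sample Size: 55% and 30% responders, two-tailed test, power 0.80, dropout 20%, 58 per group. The significance level is printed as .50; I read it as .05. From Participant Timeline and the abstract: two companies and two groups. The ICC of the 4-month response is not given, so I assume .01, .02 and .05.

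**1. The stated sample size.** At two-sided .05, the pooled formula gives 61 per arm, or 61/0.8 = 77 after dropout. The unpooled formula gives 58, or 73 after dropout. The printed level of .50 gives 18, or 23 after dropout. So 58 after dropout does not follow from the stated inputs. It appears only as the unpooled two-sided figure with no dropout added, or under a one-sided .05 level (unpooled: 46, then 46/0.8 = 57.5, rounded up to 58). That mismatch is a separate matter. What counts here is that every route to 58 is an individual-level formula with a design effect of 1.

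**2. Evaluable soldiers.** 58 × 0.8 = 46.4, taken as 46 per arm. With independent soldiers, 46 per arm has 68% two-sided power for 55% against 30%.

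**3. Clustering, if there is one company of m = 46 per arm.**

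- Design effect: DE = 1 + (m − 1) × ICC, for example 1 + 45 × .02 = 1.90.
- Effective size: 46/DE, for example 46/1.90 = 24.2.
- True type I error of the nominal 5% test: 2 × [1 − Φ(1.96/√DE)], for example 1.96/1.378 = 1.42, giving 15.5%.

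| Assumed ICC | DE | Effective n per arm | Type I error, formula | Type I error, simulated | Power if the ICC were known |
|---|---|---|---|---|---|
| .01 | 1.45 | 31.7 | 10.4% | 10.4% | 52% |
| .02 | 1.90 | 24.2 | 15.5% | 15.7% | 42% |
| .05 | 3.25 | 14.2 | 27.7% | 28.6% | 26% |

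The simulation drew beta-binomial responses at 30% in both arms. At ICC 0 it returned 5.0%, as it should.

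**4. Can more soldiers help?** With one company per arm, m grows with n, so 80% power needs n = 61 × [1 + (n − 1) × ICC], that is, n = 61 × (1 − ICC)/(1 − 61 × ICC). At ICC .01 this is 61 × .99/.39 = 155 evaluable per arm. Once the ICC reaches 1/61 = .016, no n is enough.

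**5. What the interval would look like.** Suppose the planned difference of 25 points is observed. The independent-soldier standard error is √[(.55 × .45 + .30 × .70)/46] = √(.4575/46) = .0997, so the 95% half-width is 1.96 × .0997 = 19.5 points (interval 5.5 to 44.5). Multiplying the half-width by √DE gives:

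- ICC .01: 19.5 × 1.204 = 23.5 points (1.5 to 48.5).
- ICC .02: 19.5 × 1.378 = 26.9 points (−1.9 to 51.9).
- ICC .05: 19.5 × 1.803 = 35.2 points (−10.2 to 60.2).

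From an ICC of .02 on, even the full planned effect would not exclude zero.

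**The case against.** **One company per arm is not written.** The Randomization section names no unit, the briefing of two companies is described only as a first step, and allocation by smaller units within companies is not excluded. This stands. With several smaller units per arm, m and the design effect fall and the confounding is no longer complete. The figures above hold only for one company per arm.

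**The label may be correct.** A reader might infer that nothing was randomized. The documents do not support that. Excluding individual randomization is compatible with a draw between groups, and the line manager's proposal governs which companies enter the study, not which arm they join. This is a condensed article, Figure 1 is not available, and the full protocol may describe a draw. That answers the charge of no randomization, but not the mismatch with the analysis. A draw between two companies would still leave program and company inseparable.

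**The size of the inflation is unknown.** No ICC is given, so 16% or 28% cannot be read as this trial's error rate. The primary endpoint is also a change from inclusion to 4 months, which partly removes stable company differences; the relevant ICC is that of response defined by change. Both points stand, which is why a range is shown. Events within a company between the two visits still enter that ICC, and zero is implausible given the shared setting.

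**A later analysis plan could adjust.** It could if there are several units per arm. With one per arm, the between-company variance cannot be estimated from the data, so no model supplies it.

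**Conclusion.** The point holds as an inconsistency among the stated label, the allocation and the analysis. The article claims randomization, excludes the individual form, names no other, and plans its size and primary test as if individuals had been randomized.

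The conclusions rest on different assumptions:

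- The chi-square P value is too small and the 80% power overstated if allocation was by group, as the text indicates, and the ICC of the 4-month response is above zero.
- The type I error of about 10%, 16% or 28%, and the effective size of about 32, 24 or 14 per arm, also require one company of 46 evaluable soldiers per arm and ICCs of .01, .02 or .05.
- Complete confounding of program with company requires one company per arm, which is the most natural reading but an inference.

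The text does not show that no draw took place. The matter must be settled before results are reported, because it decides whether the primary comparison can support a claim of effectiveness.

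**What to change.** 1. State the unit of allocation, the number of units per arm and the method by which units were assigned. If it is one company per arm, call the study a two-cluster, company-allocated controlled study in the title, abstract and conclusions, and limit the causal claim.
2. In that case, do not present the unadjusted chi-square P value as a valid test of effectiveness. Report the difference in response rates with intervals inflated over a stated ICC range, for example .01, .02 and .05, as a sensitivity range rather than a test. Say that the power was calculated for independent individuals and is not achieved under clustering.
3. If more than one unit per arm was allocated, analyse by the unit of allocation, using cluster-level summaries or a mixed model with a small-sample correction.

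Two tempting repairs do not serve. A random effect for workshop group is undefined in the nonintervention arm, which attends no workshops, and would not capture company variance. A draw made after baseline is useful only if allocation has not yet taken place, and the project is already under way.

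The cost is some rewording, one sensitivity analysis or a changed primary model, a weaker headline claim and wider intervals.
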